## Abstract

**Background:**

Evidence concerning the effect of Tai Chi Yunshou motor imagery training (TCY-MIT) on upper extremity motor function (UE-MF) recovery in poststroke patients is lacking, and few studies have examined the neural mechanisms of MIT. The study was designed to assess the effectiveness of TCY-MIT and its possible neural mechanisms.

**Methods/design:**

The study is an assessor-blinded, parallel, superiority, randomized clinical trial. A total of 78 eligible participants will be randomly assigned to 2 groups in a 1:1 ratio. Participants in the control group will receive (conventional rehabilitation therapies) CRTs for 40 min per day, 6 days per week, for 3 weeks. Participants in the intervention group will receive CRTs combined with TCY-MIT (30 min per day, 6 days per week, for 3 weeks). The primary outcome measure is the Fugl-Meyer Assessment of Upper Extremity. Secondary outcome measures are the Box and Block Test, muscle strength test, modified Barthel index, and Pearson correlation coefficients. All outcomes will be assessed at baseline, after completion of the intervention (1, 2, and 3 weeks), and at the end of follow-up (2 months). The outcome assessor will be blinded to the group allocation of the participants.

**Discussion:**

We expect this assessor-blinded, parallel, superiority, randomized clinical trial to explore the effectiveness of TCY-MIT combined with CRTs compared with CRTs alone for UE-MF in poststroke patients.

**Trial registration:**

Chinese Clinical Trial Registry ID: ChiCTR2100048868. Registered on 19 July 2021

**Supplementary Information:**

The online version contains supplementary material available at 10.1186/s13063-022-06283-z.

## Background

Approximately 85% of stroke survivors undergo varying degrees of upper extremity motor dysfunction [1]. Patients with residual upper limb motor deficits have poor performance in daily life activities, and more than half of them do not fully functionally recover within 6 months [2]. Some clinical rehabilitation therapies have certain requirements for patients’ muscle strength, professional guidance training and grounds, which prolong the time before a large proportion of stroke patients with upper limb dysfunction can return to family and society [3]. These results drive us to find rehabilitation therapies that are more effective and easier to handle for patients participating.

Tai Chi is a martial arts form that originated in China. It is practised in many Asian communities and has growing popularity in Western countries [4]. Practising Tai Chi improves poststroke patient independence and quality of life by relaxing joint tension, improving joint mobility, and promoting motor coordination [5]. Tai Chi Yunshou (TCY) exercise is the basic technology form of Tai Chi [6], and its motion trail is like a cloud moving through the sky, continuously without end, which includes the linkage model of upper limbs, trunk, and lower limbs [7]. Some randomized controlled trials (RCTs) have shown that TCY can effectively improve the upper limb motor function of poststroke patients [8, 9]. However, TCY exercise has certain requirements for the level of motor function of patients and professional guidance. Therefore, there is a risk that stroke patients’ ligaments and joints will be damaged when motor function and muscle strength are not in accordance with this training or with no professional guidance, so its clinical application is limited [10].

In recent years, a novel and active mental practice called motor imagery training (MIT) has emerged [11], which has been applied to all stages of stroke rehabilitation [12] and is easy to learn and master without restrictions on actual movement and training sites [11]. A meta-analysis of RCTs investigating the benefits of MIT for upper extremity motor dysfunction concluded that the clinical efficacy of the evidence supports MIT improving motor function of the upper limbs in stroke rehabilitation.

To address poststroke patients’ difficulty in performing TCY exercise, this study was designed to investigate the effectiveness of TCY combined with MIT on upper extremity motor function (UE-MF) recovery in these patients. Furthermore, there is minimal brain plasticity evidence associated with this training form. Our objective was also to explore the cortical reorganization patterns after Tai Chi Yunshou motor imagery training (TCY-MIT) in stroke patients. In this study protocol, we will describe the rationale, design, and analytic methods of an RCT designed to investigate the rehabilitative effects of Tai Chi among hospitalized stroke patients in the recovery phase. We hypothesized that poststroke patients with hemiplegic upper extremities have a better treatment and response to TCY-MIT combined with conventional rehabilitation therapies (CRTs) than individuals with CRTs treatment. Meanwhile, there will be more effective connections between damaged brain areas or between normal brain areas and damaged brain areas in the TCY-MIT combined with CRTs group.

## Methods/design

### Primary objective and study hypothesis

The primary objective of this clinical trial is to examine the therapeutic efficacy of TCY-MIT for the recovery of UE-MF in poststroke patients. The study hypothesis is that compared to CRTs, TCY-MIT associated with CRTs has a better therapeutic effect on UE-MF. It seems to be a useful complementary therapy for promoting motor function rehabilitation.

### Secondary objective

This study will also present functional near-infrared spectroscopy (fNIRS)-based resting-state imaging as a neuroimaging technique to record spontaneous brain activity for evaluating brain functional rehabilitation and to provide a precise and effective means for TCY-MIT clinical research in poststroke patients.

### Study design

This study is an assessor-blinded, parallel, superiority, randomized clinical trial (allocation ratio: 1:1). The design and report of this clinical trial protocol follow the Standard Protocol Items: Recommendations for Interventional Trials (SPIRIT) 2013 statement (Additional file 1) [13]. The schematic chart and study schedule are shown in Figs. 1 and 2.

**Fig. 1 Fig1:**
[figure not shown]
Schematic chart of the study. The template is from the CONSORT 2010 flow diagram. CRTs, conventional rehabilitation therapies; TCY-MIT, Tai Chi Yunshou motor imagery training; FMA-UE, Fugl-Meyer assessment of upper extremity; BBT, Box and Block Test; MST, muscle strength test; MBI modified Barthel index; r, Pearson correlation coefficients; FAS, full analysis set, PPS, per protocol analysis set; SAS, safety assessment set

**Fig. 2 Fig2:**
[figure not shown]
Schematic chart of the study. The schedule of enrolment, interventions, and assessments. The template is from the SPIRIT 2013 statement

### Ethical issues

Ethical approval has already been granted by the research ethics committee of Shanghai University of Traditional Chinese Medicine Yueyang Hospital of Integrated Traditional Chinese Medicine and Western Medicine (2021-020, approval received on 8 April 2021). The trial has already been registered with the Chinese Clinical Trial Registry (ChiCTR2100048868, registered on 19 July 2021). Eligible participants will be informed about this trial and sign the consent form before participating in the study.

### Sample size

The sample size was estimated based on a comparison between the intervention group and the control group, represented by the improvement of the Fugl-Meyer Assessment of Upper Extremity (FMA-UE) as the primary outcome. In this study, a two-tailed test was chosen, *α* = 0.05. *μ*_*r*_ and *μ*_*c*_ represent the mean of FMA-LE scores after treatment in the intervention group (TCY-MIT + CRTs group) and the control group (CRTs group) respectively. *K* is the ratio of the sample size between the intervention group and the control group, so *K* = 1. According to the results of previous study [14], *μ*_*r*=_47.00, *μ*_*c*_=36.00, σ = 9, Δ = 3.6, *Z*_1 − *α*_= 1.96, and *Z*_1 − *β*_= 1.28. The calculated sample size of each group was approximately 32 individuals to achieve a power of 0.90 at a significance level of 0.05. After accounting for an anticipated dropout rate of 20%, the total number of patients required for this trial was 78, with 39 in each group. The formulas are as follows:
$$ {\displaystyle \begin{array}{c}{n}_r=\mathrm{K}{n}_c\\ {}{n}_c=\frac{{\left({Z}_{1-\alpha }+{Z}_{1-\beta}\right)}^2{\sigma}^2\left(1+\frac{1}{k}\right)}{{\left({\mu}_r-{\mu}_c-\Delta \right)}^2}\end{array}} $$

where *μ*_*r*_ is the mean of the intervention group, *μ*_*c*_ is the mean of the control group, *K* is the ratio of the sample size between the intervention group and the control group, Δ is the margin of superiority, and σ is the standard deviation.

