### Primary outcome measure

#### Motor function

The primary outcome measure is a change in score on the Fugl-Meyer Assessment of Upper Extremity (FMA-UE). The FMA-UE has been used to assess MIT-induced changes in upper extremity motor impairment in numerous RCTs [17, 18]. The acquired data are in the form of a 3-point ordinal scale (0 = cannot perform at all; 1 = can perform partially; 2 = can perform fully) that is calculated for each item [16]. The scale contains a total of 33 items, which are summed to provide the maximum score of 66. Assessors evaluated all participants immediately before therapy, after 3 weeks of therapy, and at the end of follow-up.

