### Statistical analysis

A sample size of 64 participants (32 per group) was determined to provide 90% power (*α* 0·05) to detect a mean FMA-UE difference of 11.0 (SD 9) points between the two treatment groups. The main analysis of this trial consists of a comparison of the outcomes after 3 weeks and at the end of follow-up (2 months). The statistician who is blinded to the group allocation of the participants will lock all data before statistical analysis. All data will be analysed with Social Sciences (SPSS) version 26.0 software (IBM Corporation, Armonk, USA) and GraphPad Prism version 9.0 software (GraphPad Software Inc., San Diego, USA). The baseline data and outcome analyses will be conducted on the full analysis set (FAS), using intent-to-treat (ITT) samples and completer samples. The per protocol set (PPS) will be used to analyse effective cases based on FAS. Furthermore, safety analysis will be performed on safety assessment set (SAS). Demographic data will be analysed using a two-sample *t*-test or Wilcoxon rank-sum test for continuous variables and the chi-squared test or Fisher’s exact test for categorical variables. For outcome, variables will be presented as the mean ± standard deviation ($$ \overline{x}\pm \mathrm{s} $$). Primary outcomes and secondary outcomes will be analysed using multivariable analysis of variance (ANOVA) for repeated measures, followed by Tukey's post hoc test. Statistical significance will be set at a *P value* less than 0.05.

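### The sample size uses post-treatment FMA-UE means with an SD of unstated scale, while the primary outcome is change analysed without a baseline covariate; adjusting for baseline would remove the dependence on an unknown correlation

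*Protocol article*

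**What the plan says.** Three sections of the protocol article bear on this point.

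- **Sample size.** The calculation is introduced as "represented by the improvement of the Fugl-Meyer Assessment of Upper Extremity (FMA-UE) as the primary outcome". The two means, 47.00 and 36.00, are then said to "represent the mean of FMA-LE scores after treatment" (FMA-LE is evidently a slip for FMA-UE). The other inputs are "σ = 9, Δ = 3.6", where Δ "is the margin of superiority, and σ is the standard deviation". The text says "a two-tailed test was chosen", and about 32 per group are needed "to achieve a power of 0.90 at a significance level of 0.05". Allowing for 20% dropout gives 39 per group, 78 in total.
- **Motor function (Primary outcome measure).** "The primary outcome measure is a change in score on the Fugl-Meyer Assessment of Upper Extremity (FMA-UE").
- **Statistical analysis.** "Primary outcomes and secondary outcomes will be analysed using multivariable analysis of variance (ANOVA) for repeated measures", with Tukey's test to follow. No baseline covariate is named. The same section restates 90% power for 64 participants to detect a difference of 11.0 points (SD 9), without mentioning the 3.6 margin.

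The article gives neither a baseline SD nor a correlation between baseline and post-treatment FMA-UE.

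**The concern.** The means are on the scale of post-treatment scores, whereas the primary outcome is on the scale of change. Under randomisation the expected group difference is the same on both scales, so the 11 points can carry over. The SD does not carry over. If 9 is the spread of post-treatment scores, the spread of change may be larger or smaller, depending on how strongly baseline predicts the later score. The stated 90% would then belong to a different analysis from the one declared primary.

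Precision is also at stake. Baseline FMA-UE is already measured, and Brunnstrom grades II to VI admit a wide range of initial impairment. With about 64 patients analysed, chance baseline imbalance can matter. A change score corrects for it with a fixed slope of 1, whether or not that slope fits the data.

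**Working it through.** **1. Inputs from the Sample size section.** Means 47.00 and 36.00; SD 9; margin 3.6; z values 1.96 and 1.28; equal allocation.

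**2. The plan's own figure reproduces.** n per group = (1.96 + 1.28)² × 9² × 2 / (11 − 3.6)² = 10.4976 × 162 / 54.76 = 31.06, rounded up to 32. With 32 per group and the t distribution, power for a net difference of 7.4 is 89.9%. Without the margin the formula gives 10.4976 × 162 / 121 = 14.05, or 15 per group. So 32 per group at 90% power belongs to the margin test.

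**3. Assumptions that the article does not supply.** SD 9 is the post-treatment SD; the baseline SD is also 9; the baseline to post-treatment correlation is ρ, taken over a range.

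**4. SDs of the two analyses.**
- Change score: 9 × √(2(1 − ρ)). At ρ = 0.3 this is 9 × √1.4 = 10.65.
- Post-treatment score with baseline as covariate (ANCOVA): 9 × √(1 − ρ²). At ρ = 0.3 this is 9 × √0.91 = 8.59.

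**5. Power against the 3.6 margin** (net difference 7.4, 32 per group, two-sided 0.05, noncentral t):

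| ρ (assumed) | SD of change | Power, change | ANCOVA SD | Power, ANCOVA |
|---|---|---|---|---|
| 0.3 | 10.65 | 78.1% | 8.59 | 92.4% |
| 0.4 | 9.86 | 84.0% | 8.25 | 94.2% |
| 0.5 | 9.00 | 89.9% | 7.79 | 96.2% |
| 0.7 | 6.97 | 98.7% | 6.43 | 99.5% |

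At ρ = 0 ANCOVA gives 89.9%, the planned figure. By the normal approximation, the change score reaches 90% power at ρ = 0.485 with 32 per group and at 0.501 with 31 (39 less 20%).

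**6. Sensitivity to the baseline SD.** If the baseline SD is s, the variance of change is 81 + s² − 18ρs. This stays at or below 81 only if ρ ≥ s/18: 0.39 for s = 7, 0.50 for s = 9, 0.61 for s = 11.

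**7. Power against zero, 11.0 points, 32 per group.** The change score has 92.5% power at ρ = 0 with the t distribution. The normal approximation gives 93.3% at ρ = 0, 98.5% at 0.3 and 99.8% at 0.5. On this reading the 90% is met at every non-negative ρ.

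**8. Precision.** The standard error is SD × √(2/32) = SD × 0.25. With a t quantile of about 2.0, the 95% CI half-width at ρ = 0.3 is 10.65 × 0.25 × 2.0 ≈ 5.3 for change and 8.59 × 0.25 × 2.0 ≈ 4.3 for ANCOVA. With equal SDs the variance ratio of change to ANCOVA is 2(1 − ρ)/(1 − ρ²) = 2/(1 + ρ): 1.54 at ρ = 0.3, 1.33 at 0.5, 1.18 at 0.7.

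**The case against.** A reader might infer that the trial is underpowered, or that its 90% holds only if the correlation is at least 0.5. The documents do not support either reading, for four reasons.

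- **The threshold needs the margin.** The Statistical analysis section names no test against 3.6 and quotes 11.0 points. For that test, power on change is adequate at any non-negative correlation. This stands. It does not settle the matter, because 32 per group follows only from subtracting 3.6, so the two sections disagree about which test has 90% power.
- **SD 9 may already be an SD of change.** The article calls it only the standard deviation. This also stands: the post-treatment reading is an inference from the means beside it, and the protocol should not be told to declare it as fact or as an upper bound.
- **The correlation may well exceed 0.5.** The same scale is repeated three weeks apart in patients 3 to 6 months after stroke, with widely varying impairment. That is plausible, and a change analysis would then have more power than planned. But the article gives no correlation in either direction.
- **The model and its covariates could be left to an analysis plan.** Change is unbiased under randomisation, and a repeated-measures ANOVA with baseline as a time level does use baseline through the group-by-time contrast. The power figures above are for two-sample comparisons at 3 weeks, not for that full model. A missing covariate alone would therefore be no finding. What remains is that the article itself states the sizing inputs, the outcome and the model, and that these do not agree.

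The precision gain is also conditional in size. Change equals ANCOVA in precision when ρ × SD(post)/SD(baseline) = 1; otherwise, apart from the one degree of freedom spent, ANCOVA is more precise.

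**Conclusion.** The mismatch between the sizing scale and the primary outcome is in the text and should be reconciled. Its effect on power is conditional. If SD 9 is a post-treatment SD, the baseline SD is equal and the test is against 3.6, a change-score comparison falls to 78% at a correlation of 0.3 and exceeds the plan at 0.7, with break-even near 0.5. If the test is against zero, no shortfall arises at any non-negative correlation. A loss of power is therefore possible but not demonstrated.

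The case for baseline adjustment does not depend on settling this. Under the same assumptions it keeps power at about 90% or more for every non-negative correlation. It is a worthwhile improvement to the plan; it does not correct a proven failure.

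**What to change.** 1. **Motor function and Statistical analysis.** Define the primary comparison as 3-week FMA-UE between groups with baseline FMA-UE as a covariate, by ANCOVA or by a mixed model of the post-baseline visits with baseline as covariate. Report the adjusted difference with its 95% CI.
2. **Sample size.** State from the cited source study whether SD 9 is the SD of post-treatment scores or of change, and correct FMA-LE to FMA-UE.
3. **Sample size and Statistical analysis.** Make the two sections agree on whether the 90% power refers to the test against the 3.6 margin. If it does, name that test in the analysis; if not, remove the margin from the calculation.

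The cost is wording only. Baseline FMA-UE is already scheduled, so no patients, visits or data are added, and the adjusted difference estimates the same treatment effect as the difference in change.

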### Setting and recruitment

This trial will be conducted from August 2021 to April 2022 at the rehabilitation department, Shanghai University of Traditional Chinese Medicine Yueyang Hospital of Integrated Traditional Chinese Medicine and Western Medicine, Shanghai, China. The study will be mainly recruited through WeChat promotions, posters, and promotional leaflets with the inclusion criteria of the trial. A total of 78 participants who meet the eligibility criteria will voluntarily participate in the trial and sign the informed consent form that has been approved by the ethics committee before enrolment.

### Eligibility criteria

#### Inclusion criteria

First event of stroke (infarct or haemorrhage) and in line with the diagnostic criteria of cerebrovascular disease formulated by the 4th National Cerebrovascular Academic Conference, confirmed by CT or MRI;No gender limitation, age 40 to 80 years;Poststroke duration 3 to 6 months;For pure motor hemiplegia, the degree of affected upper and hand is Brunnstrom grade II–VI;Good MI ability assessed by the Kinesthetic and Visual Imagery Questionnaire (KVIQ-20) ≥ 25;Right-handed, as determined by the Edinburgh Handedness Inventory;Agreement of the patient or his or her legal guardian (if necessary) to voluntarily participate in the study and signed informed consent. Able to understand and implement rehabilitation training.

#### Exclusion criteria

Unable to perform MIT;Unable to communicate or unable to follow commands;Severe speech, attention, hearing, vision, intelligence, mental or cognitive impairment (MMSE < 27);Current participation in any experimental study;Unable to cooperate complete training and evaluation for any reason;Serious primary or secondary diseases, such as severe liver and kidney haematopoietic system disease, severe cardiopulmonary insufficiency, and arrhythmia.

### Randomization and blinding

All eligible participants will be randomly assigned to two groups in a 1:1 ratio. The computer-generated randomization sequence numbers will be generated using the Statistical Package for the Social Sciences (SPSS) 26.0 statistical software. This work will be performed by an occupational therapist not involved in this trial and kept in sealed envelopes. The occupational therapist will assign participants to the two groups according to the random sequence.

To minimize the source of bias after randomization, we will take the following method during this research: conventional rehabilitation therapists and participants will not have any information about the purpose of this study and whether other treatments will be conducted. Meanwhile, TCY-MIT will be guided by another therapist who will not know whether the patients’ participating in other therapies. Furthermore, participants and research personnel do not know the allocated group. The outcome assessor would not be involved in the whole therapy process. Additionally, to examine the success or failure of blinding, an assessor will be evaluated by calculating new blinding index (BI) [15]. They will be inquired which group do they think patients take part in and choose one item from the following answers: CRTs group, TCY-MIT group, or unknown. The new BI is scaled to an interval of − 1 to 1 (0 = consistent with perfect blinding; 1 = complete lack of blinding; -1 = opposite guessing which may be related to unblinding). If a higher-than-expected proportion guesses correctly, a discussion will be made concerning the potential biases causing partial unblinding.

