#### Intervention group

The participants in the intervention group will also accept CRTs, which are identical to the control group. The difference between the two groups is that the intervention group will perform TCY-MIT for 30 min per day, 6 days per week, for 3 weeks. The TCY-MIT consists of 4 steps, and the process is as follows.
Step 1: Participants will be organized to watch a video of the TCY exercise movement. The trained TCY therapists will demonstrate the movement of A to F (Fig. 3) and teach the participants to perform TCY exercise with their affected upper limb.Step 2: Participants will wear headphones and relax by listening to soft music for 4 min.Step 3: Participants will undergo 24 min of imagining the TCY exercise with instructions. Participants will be asked to apply kinesthetic images (first-person images) related to using the affected upper limb.Step 4: In the final 2 min, participants will be allowed to refocus on the room.

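### The blinding section says participants and research personnel are unaware of allocation, which an openly delivered one-arm add-on does not support; the claim should be limited to the assessor, statistician and fNIRS technician

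*Protocol article*

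**What the plan says.** The Randomization and blinding section of the protocol article makes two broad claims. The first is that "conventional rehabilitation therapists and participants will not have any information about the purpose of this study and whether other treatments will be conducted". The second is that "participants and research personnel do not know the allocated group". It adds that the therapist guiding TCY-MIT will not know whether patients receive other therapies. It also plans a blinding index, computed from the assessor's guesses only.

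Other sections bear on these claims:

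- **Ethical issues:** "Eligible participants will be informed about this trial and sign the consent form before participating in the study". Setting and recruitment likewise has participants "sign the informed consent form that has been approved by the ethics committee before enrolment".
- **Intervention group:** "The difference between the two groups is that the intervention group will perform TCY-MIT for 30 min per day". The sessions consist of a video with demonstration and teaching, relaxation to music through headphones, guided imagery, and a short refocusing period. A trained occupational therapist administers them.
- **Control group:** conventional rehabilitation only, 40 min per day on the same schedule. Nothing is described in place of TCY-MIT.
- **Abstract and Study design:** the trial is labelled assessor-blinded. Outcome measures and follow-up repeats the assessor's blinding, Statistical analysis adds the statistician, and the Discussion adds the fNIRS technician.

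**The concern.** The blinding section states a property that the described treatments do not provide, and it goes further than the trial's own label. This matters because the clinical outcomes depend partly on what the patient does in the test. FMA-UE items are scored on performance, the Box and Block Test asks for as many blocks as possible, and grip and pinch ask for maximal force. Expectation and effort can influence such measures, and a patient who mentions the imagery sessions can unblind the assessor.

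A reader who accepts the sentence would set expectation aside as an explanation for a group difference, and the design gives no ground for doing so. The planned check would not correct that reader, because it does not question participants or treating therapists.

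**Working it through.** No formula applies to the blinding claim, so the check sets the sections side by side, group by group.

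**1. The therapist delivering TCY-MIT.** TCY-MIT is what separates the arms, and only the intervention arm receives it. Anyone who delivers it therefore knows the allocation of each person treated. The safeguard offered is that this therapist does not know about other therapies. That hides whether the patient also receives CRTs, which both arms do, and it does not hide the arm. This conclusion needs no assumption about consent.

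**2. Conventional therapists.** They are to be kept unaware of the purpose and of other treatments. Because CRTs are identical in both arms, this is feasible unless patients tell them.

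**3. Participants.** The sequence in the article is:

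- Recruitment uses "WeChat promotions, posters, and promotional leaflets with the inclusion criteria of the trial".
- One of those criteria is "Good MI ability assessed by the Kinesthetic and Visual Imagery Questionnaire (KVIQ-20) ≥ 25", so motor imagery is visible at the entry stage for both arms.
- Participants are informed about the trial and sign consent.
- One arm then has 6 days × 3 weeks = 18 guided imagery sessions, and the other has none.

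A participant who knows from consent that imagery training is under test can tell the arm from whether the sessions take place. A participant who was told nothing about the arms might not. The article does not say what the form discloses, so the inference is probable and not certain. In either case, having no information about the purpose of the study sits uneasily with being informed about the trial.

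**4. Assessor, statistician and fNIRS technician.** None is described as delivering treatment, and the assessor is kept out of the therapy process. Blinding of these three roles remains feasible.

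**5. Scheduled treatment.** This is a separate feature of the comparison and does not measure bias.

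- Control arm: 18 × 40 = 720 min.
- Added in the intervention arm: 18 × 30 = 540 min.
- Steps 2 to 4 of the session: 4 + 24 + 2 = 30 min. They fill the stated half hour without Step 1, the video and teaching.
- The article does not say whether Step 1 falls within the 30 min or is repeated at each session. The extra time is therefore best stated as at least 30 min per day.

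**6. Sample size.** The figures of 32 per group and 78 in total do not rest on who is blinded and are unaffected.

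**The case against.** The strongest case on the other side has four parts.

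- **The label is already right.** The trial is called assessor-blinded in the Abstract and in Study design, and nowhere is it labelled participant-blinded. This stands. A reader might infer that the trial will be reported as participant-blinded, but nothing in the document says so. The overstatement is confined to the Randomization and blinding section.
- **Participants might truly be unaware.** A patient can know what treatment is being received without knowing that another arm exists or which one is experimental. This also stands in part. A reader might infer that participant blinding is impossible, but that depends on a consent form that is not shown. Nor do the recruitment materials disclose the purpose: the article says only that they carry the inclusion criteria.
- **Research personnel may not include therapists.** The section treats therapists in separate sentences, so the term is ambiguous. An ambiguous claim still needs narrowing, because its plain reading covers the person delivering TCY-MIT.
- **Safeguards exist.** The primary outcome is scored by a blinded assessor, participants cannot see their grip and pinch results, and the blinding index could pick up an assessor unblinded by patients. These reduce the risk. They do not address patient effort or expectation, and the index detects unblinding of the assessor without preventing it.

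The add-on comparison itself is stated openly in the Abstract and in the study hypothesis, so only the looser sentence giving the primary objective needs rewording.

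**Conclusion.** The point holds in a limited form. The blinding statement is wrong for the therapist who delivers TCY-MIT, on the document's own description. For participants it is unsupported and probably wrong; that part assumes that being informed about the trial includes some mention of the imagery training or of the two arms. It goes beyond the assessor-blinded label used elsewhere, and it conflicts with the consent text until the two are reconciled.

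The consequence is for interpretation: a group difference on effort-dependent outcomes cannot be presented as free of expectation effects. The size of any such effect cannot be computed from the document. It is tempting to use the ratio of scheduled times, (40 + 30)/40 = 1.75, as a measure of the bias. The document does not support that: treatment time is a different matter from a false blinding claim, the ratio says nothing about expectation or disclosure, and it depends on where Step 1 falls.

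**What to change.** - In Randomization and blinding, limit the claim to the outcome assessor, the statistician and the fNIRS technician. State that TCY-MIT therapists are not blinded and that participants cannot be assumed to be.
- Reconcile the sentence on withholding the study's purpose and other treatments with Ethical issues and with Setting and recruitment, saying what participants are told at consent.
- Instruct participants not to reveal their treatment to the assessor.
- In Primary objective and study hypothesis, word the conclusion to be drawn as the effect of adding TCY-MIT to CRTs versus CRTs alone, without participant blinding and with at least 30 min per day more scheduled treatment in one arm.

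The cost is a few sentences, one instruction to participants and a more modest conclusion. Sample size, outcomes and analysis stay as they are.
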